#### Population

All babies born at 27–31 weeks gestation between 1 January 2014 and 31 December 2018, in an English hospital with an LNU or NICU, whose records are captured within the National Neonatal Research Database (NNRD) will be included. With approximately 6000 babies per year in England meeting our criteria, the study is expected to include data on approximately 30 000 babies. Data on births and transfers to and from an SCBU will also be captured, to provide baseline information of place of birth, care and transfer across all neonatal units in England for this gestational age range.

Data sources:

Neonatal data: The NNRD will provide data on admissions to LNU or NICU in England. The NNRD is maintained by the NDAU and created from electronic health records.^21^ It includes the information on characteristics of mothers and babies (eg, maternal pregnancy information, baby’s birth weight, sex and gestational age), admission-related episodes (eg, reason for admission, admission temperature, length of stay and the number of episodes of care) and daily neonatal care of the babies after birth (eg, treatment, clinical procedures and morbidities).Postneonatal data: To assess outcomes (survival and morbidities) to 365 days of age, the NNRD data will be linked to:Hospital Episode Statistics (HES): information all admissions, outpatient appointments and accident and emergency attendances at NHS hospitals in England.Office for National Statistics (ONS): information on location, date and cause of death, obtained from death registration records.

Neonatal units will be allowed to assess the quality of their data entry onto electronic records, based on completion of data being fed back to neonatal units for surfactant replacement, nitric oxide and discharge home on oxygen.

Inclusion and exclusion criteria: Units will be offered an opt-out option at the start of the project. The confidentiality of neonatal units who chose to opt out will be respected. A minimum dataset describing these units will only be reported if it is possible to maintain their anonymity in this process.

Clinical outcomes: The primary outcome for workstream 1 is death before discharge from a neonatal unit. We expect a within-unit mortality percentage of approximately 5% in this group. Information on deaths outside of neonatal care will be provided from ONS.

Secondary outcomes (eg, bronchopulmonary dysplasia, retinopathy of prematurity requiring laser treatment and worst cranial ultrasound abnormalities)^22^ will be extracted from the daily care records in the NNRD. Data will be investigated for inconsistencies, out of range values and missing observations prior to the analysis of workstream 1. Special attention will be paid to morbidities that may be more relevant to this group of babies, such as growth during hospitalisation, blood stream infections, patent ductus arteriosus, time to full enteral feeds, time to breast feeding at initiation and breast feeding at discharge.

Statistical methods: In the absence of randomised treatment allocation, the difference in mean outcomes of babies born in either setting with an NICU or an LNU might be biassed if they are different in baseline characteristics, that is, our data sources are subject to selection bias. The analysis needs to account for the potential bias arising from the non-random allocation of babies to the two types of ‘interventions’. We will tackle these issues in our analysis using matching and instrumental variables (IVs) methods. The same approaches will be followed by workstreams 1 and 3.

Matching to account for measured confounding: We will use matching to construct a balanced sample of babies who were born in NICU or LNU based on observed characteristics, assuming that these groups do not differ in relevant unobservable characteristics so that the differences in outcomes between them may be attributed to the location of birth. We will use propensity scores (PS), which are predicted probabilities of the relevant observed covariates that would be expected to be equal for both groups if the conditional distribution is independent of whether the baby is born in an NICU or LNU.^23 24^ To compute the PS, a logistic model for place of birth will be fitted (LNU vs NICU). The independent variables will include a priori decided set of variables on the basis of expert and clinician input and/or variables associated with the type of unit at the place of birth. Based on previous literature^25 26^ and the data availability in NNRD, we will evaluate a relatively large number of covariates for this model including: gestational age, birth weight, sex of the baby, mothers’ ethnicity, use of antenatal steroids, 5 min Apgar score, deprivation, temperature at birth, maternal medical problems prior to this pregnancy and problems encountered during pregnancy. The selected variables are expected to influence either the place of birth or babies’ outcomes, but none of them would be expected to be influenced by whether the baby is born in an NICU or LNU as they are defined at baseline prior to or immediately after the birth. We believe that the model developed in the above steps will produce the PS given the observed set of covariates to produce balanced groups for the analyses; this means that babies who were born in NICUs and those who were born in LNUs with equal PS will have the same distributions of the observed covariates. After the PS is computed from the model, a matched sample will be created and the covariates will be compared between the groups in the matched sample to examine whether the balance has been achieved or not. If the sufficient balance is not achieved, the PS model will be modified and balance will be reassessed. We will investigate the range of estimated PS for both NICU and LNU babies to identify the region of common support. If there is no comparable NICU baby found in the LNU group, the analyses would produce biassed estimates by matching LNU babies with NICU babies with different characteristics. Therefore, observations not under common support should be dropped from the matching, but we will describe the characteristics of these babies in descriptive statistics. It is difficult to define the size of this matched sample at this stage. The sample size will be affected by how relevant it will be considered to the general population and will be reviewed by the study team. If required, other matching methods will also be applied, such as Mahalanobis distance matching and genetic matching.^27^

IVs to account for unmeasured confounding: Since matching is based on the assumption that the place of birth is independent of the potential outcomes conditional on the matching variables (also known as measured confounding). This requires that variables that affect both outcomes and the place of birth are observed and controlled in the matching algorithm. In our case, after matching the babies who were born in NICU or LNU on the basis of observed characteristics, it is possible that unobserved confounding variables still remain unbalanced between the two groups and the matching would result in biassed estimates of the effects of being born in NICU compared with LNU. Although we believe that the richness of our dataset makes the assumptions behind the matching plausible, we will complement our analyses using IVs.^28^ We will explore two-stage least squared regression (2SLS) models with exclusion restrictions that help us to explain variation in the types of unit the babies were born that is independent of outcomes. In the first stage, we will estimate the probability of a baby’s birth in NICU as a function of baby-level characteristics and IVs. The estimated probability of being born in an NICU will then be used in a second equation to estimate the effect of being born in an NICU on the outcomes of interest after controlling for a vector of observed baby-level characteristics. If the IVs are correct, the 2SLS method will generate unbiased estimates of the place of birth on babies’ outcomes.

In general, a variable is considered to be an IV, if it is (1) associated with the type of unit at birth (NICU vs LNU), (2) does not have direct effect on the outcome (say mortality) and (3) is independent of unmeasured confounders (UCs) but may be related to the measured confounders (MCs).^28 29^ The assumed relation of (IV) with outcome (4), type of unit at birth (NICU vs LNU), UCs and MCs can be described by the graph in figure 3.^30^

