**Methods:**

In this mixed-methods study, our primary objective is to assess, for babies born at 27–31 weeks gestation and admitted to a neonatal unit in England, whether care in an NICU vs an LNU impacts on survival and key morbidities (up to age 1 year), at each gestational age in weeks. Routinely recorded data extracted from real-time, point-of-care patient management systems held in the National Neonatal Research Database, Hospital Episode Statistics and Office for National Statistics, for January 2014 to December 2018, will be analysed. Secondary objectives are to assess (1) whether differences in care provided, rather than a focus on LNU/NICU designation, drives gestation-specific outcomes, (2) where care is most cost-effective and (3) what parents’ and clinicians' perspectives are on place of care, and how these could guide clinical decision-making. Our findings will be used to develop recommendations, in collaboration with national bodies, to inform clinical practice, commissioning and policy-making. The project is supported by a parent advisory panel and a study steering committee.

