**Figure 2 F2:**
[figure not shown]
Overview of OPTI-PREM workstreams. BAPM, British Association of Perinatal Medicine; LNU, local neonatal unit; NICU, neonatal intensive care unit; NNRD, National Neonatal Research Database; ODNs, operational delivery network;

Workstream 1: Clinical outcomes study

Workstream 1 aims to determine whether the type (designation) of unit (NICU vs LNU) at birth influences the primary outcome (mortality) and secondary outcomes (morbidities) in babies born at 27–31 weeks gestation.

Workstream 2: study of clinical care provided in different neonatal units

Variation exists in how neonatal units manage preterm babies of all gestational ages, even among units of the same designation.^15–18^ In this workstream, we will address the secondary objective of identifying key differences in unit characteristics and clinical practices that could influence outcome. This will allow us to group neonatal units based on care provided, and to search for associations with gestation specific outcomes, irrespective of their designation.

Workstream 3: cost-effectiveness analysis

The health economics analysis investigates whether being born in settings with an NICU or LNU represent value for money within the National Health Service (NHS). A detailed cost analysis of the neonatal care received will be carried out. An incremental analysis of costs and the number of lives saved between different locations of birth will also be conducted.

Workstream 4: ethnographic study with parents and clinicians

Using an ethnographic approach that accesses their lived experiences^19 20^ of caring for these babies, this stream explores parents' and clinicians’ experiences and perspectives regarding decisions about place of care.

Workstream 5: collaboration with the British Association of Perinatal Medicine (BAPM) to establish framework documents and recommendations on place of birth.

A working group will be established in collaboration with BAPM, which will engage with relevant stakeholders, the BLISS parent advisory panel and other support groups. Its purpose will be to establish a framework document and design recommendations for place of birth for babies born at each week of gestation between 27 and 31 weeks, based on the evidence from this study.

### Workstreams 1 and 3

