XA03Z	Neonatal critical care, special care, carer not resident alongside baby	£605
XA04Z	Neonatal critical care, special care, carer resident at cot side and caring for baby	£435
XA05Z	Neonatal critical care, normal care	£441
XA06Z	Neonatal critical care, transportation	£1159

HRG, Healthcare Resource Group; NHS, National Health Service.

The costs of standard care provided by NICU or LNU, unit costs will be multiplied by the number of days using different levels of care. Since the standard packages costed by HRG codes do not include all major clinical activities, we will also cost the use of selected relevant procedures. These will include nitric oxide, surfactant replacement, total parental nutrition, ultrasound scanning, blood transfusion and palivizumab therapy. Cost data for these activities will be obtained from literature reviews and extracted from selected hospital finance departments as needed. The cost of surgical procedures are included in the standard care package by the level of care defined by HRG codes and will not be costed separately. Key components of healthcare resource use will be presented separately from associated costs as currently recommended.

Original neonatal care information will be linked to HES to extend the time horizon of the economic evaluation to 1 year of corrected age. A comprehensive cost analysis using the methodology above will be conducted to identify whether patterns of service use of hospital admissions, outpatient visits and accident and emergency services differs across neonatal strategies at 1-year-follow-up.

The number of lives saved will be the health outcome measure that will be used in the economic evaluation. Deaths occurring after discharge from the neonatal unit will be informed by the ONS linked. An incremental analysis of costs and health outcomes between NICUs and LNUs will be conducted and synthesised using the net-benefit framework. Current thresholds of willingness to pay as recommended by the National Institute for Health and Care Excellence (NICE) will be used to determine value for money.

We will follow current guidance for methods of technology appraisal to present and report the results of the economic analysis.^31–33^

### Workstream 2

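### The primary objective runs to 1 year, but the workstream 1 primary outcome ends at neonatal discharge and 365-day mortality is not named among its ranked outcomes

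*Protocol article*

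**What the plan says.** The abstract (Methods) gives the primary objective as assessing "whether care in an NICU vs an LNU impacts on survival and key morbidities (up to age 1 year), at each gestational age in weeks". The data-sources text under Workstreams 1 and 3, Population, shows that the 1-year horizon covers survival as well as morbidity: "To assess outcomes (survival and morbidities) to 365 days of age, the NNRD data will be linked to" HES and ONS.

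The clinical-outcomes paragraph of the same section then states: "The primary outcome for workstream 1 is death before discharge from a neonatal unit". The next sentences expect about 5% within-unit mortality and add: "Information on deaths outside of neonatal care will be provided from ONS". The workstream 1 aim, in the overview of workstreams, gives no horizon. It asks whether unit type at birth "influences the primary outcome (mortality) and secondary outcomes (morbidities) in babies born at 27–31 weeks gestation". The secondary outcomes are to be taken from the NNRD daily care records, and the examples listed are morbidities, growth and feeding.

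For workstream 3, the health outcome is lives saved, and "Deaths occurring after discharge from the neonatal unit will be informed by the ONS linked". The same part of the article plans to "extend the time horizon of the economic evaluation to 1 year of corrected age".

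**The concern.** The article states both an objective and a primary outcome, and their horizons differ. A baby who dies after leaving neonatal care but before the first birthday counts as a survivor in the primary analysis and as a death under the primary objective. No other named workstream 1 outcome closes that gap.

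Discharge also has no fixed age. The phrase 'a neonatal unit' does not say whether the window closes at the first unit's discharge, at a transfer, or at final discharge from neonatal care. The background section says that transfers depend partly on cot capacity and staffing, and the workstream 2 outline says that management varies between units. Matching and two-stage least squares deal with non-random place of birth. They do not equalise the length of the window.

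At stake is whether the recommendations on place of birth rest on survival to discharge or on survival to 1 year. A second risk is that workstreams 1 and 3 report different mortality contrasts for one cohort without the reader being told why.

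**Working it through.** **1. The plan's own figure.** About 6,000 babies a year × 5 years (2014–2018) = 30,000, which reproduces the stated cohort. At the expected 5%, in-unit deaths are 0.05 × 30,000 = 1,500, leaving 28,500 babies alive at discharge.

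**2. Horizons side by side.**

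| Place in the protocol article | Horizon for survival |
|---|---|
| Abstract, primary objective | up to age 1 year |
| Workstream 1 aim | none given |
| Workstreams 1 and 3, purpose of linkage | 365 days of age |
| Workstreams 1 and 3, primary outcome | discharge from a neonatal unit |
| Workstream 3, economic evaluation | 1 year of corrected age |

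Reading the 1-year limit in the objective as applying to morbidities alone fails, because the linkage sentence names survival explicitly. The last row also differs from the third: corrected age is counted from a later date than birth for a preterm baby, so the two limits do not coincide.

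**3. Deaths outside the primary outcome (assumed range).** The documents give no mortality after discharge. Let q be mortality from discharge to 1 year among the 28,500. Then extra deaths = 28,500 × q, and the share of 1-year deaths outside the primary outcome = extra / (1,500 + extra).

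| q (assumed) | Extra deaths | 1-year mortality | Share outside primary outcome |
|---|---|---|---|
| 0.25% | 71 | 5.24% | 4.5% |
| 0.5% | 142 | 5.48% | 8.7% |
| 1.0% | 285 | 5.95% | 16.0% |
| 1.5% | 428 | 6.43% | 22.2% |

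These deaths would be held in the ONS data. They are outside the primary outcome, not lost to the study.

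**4. When the two contrasts would part (illustration).** Let M be 1-year mortality, the same in both settings, and f the share of those deaths that fall after discharge. In-unit mortality = M × (1 − f). Take M = 6%:

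- f = 10% in both: 5.4% against 5.4%, no artefact.
- f = 10% and 15%: 6% × 0.90 = 5.4% against 6% × 0.85 = 5.1%, a difference of 0.3 points.
- f = 10% and 20%: 5.4% against 6% × 0.80 = 4.8%, a difference of 0.6 points.

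Use a simple comparison of two independent proportions with an assumed 15,000 per group. For the 0.6-point case, SE = √(2 × 0.051 × 0.949 / 15,000) = 0.00254 and z = 0.006 / 0.00254 = 2.36. A two-sided 5% test would be significant about 66% of the time. For the 0.3-point case, z is about 1.2 and the figure is about 21%. With 10,000 per group the 0.6-point case gives z of about 1.93. With 3,000 per group (30,000 / 5 weeks / 2 groups, if spread evenly) it gives about 1.06. The splits and the group sizes are assumptions, and the article says that the matched sample size cannot yet be defined.

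**The case against.** The strongest reply is that most of the remedy is already planned. ONS supplies date, location and cause of death, the linkage exists to assess survival to 365 days, and deaths outside neonatal care are mentioned directly after the primary outcome. On this view only the ranking of two mortality measures is open. An objective may be broader than its single primary outcome, and the 1-year wording of the objective comes from the abstract (the figure that summarises the objectives is not shown). Survival to discharge is also the benchmark in the 23–26 week evidence that the article cites, so keeping it gives comparability. It also avoids dependence on linkage completeness. An economic horizon longer than the clinical one is not a defect in itself.

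Much of this stands. Death before discharge is a defensible primary outcome, and replacing it is a trade-off. What does not fall away is that the article names no ranked workstream 1 outcome for the 1-year survival question that its primary objective asks.

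A reader might go further and infer that the discharge endpoint is biased between NICU and LNU births. The documents do not support that. Nowhere do they say that discharge timing or place of death differs by birth setting, and the variation that they report exists even within a designation. Nor do they show that step-down cuts follow-up short: an SCBU is itself a neonatal unit, SCBU transfers are captured, and exposure is fixed by unit type at birth.

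**Conclusion.** The mismatch between objective and primary outcome is in the text and needs no assumption. The survival part of the primary objective runs to 1 year, the workstream 1 primary outcome stops at a discharge of no fixed age, and 365-day mortality is not named as a ranked workstream 1 outcome.

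The size of any consequence cannot be derived from the documents. If mortality after discharge lies between 0.25% and 1.5%, some 71–428 deaths, or 4.5–22% of deaths by 1 year, fall outside the primary outcome. The NICU–LNU contrast is distorted in the way shown only if the share of deaths after discharge differs between birth settings. The 5.4% against 5.1–4.8% example shows the mechanism and does not estimate it. In particular, the z of 2.36 should not be read as a predicted false finding, because it rests on an invented 10% and 20% split and an assumed 15,000 per group.

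This should be put right because the data are already being collected and the change lets the study answer its own question.

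**What to change.** - Name all-cause death by 365 days, from the ONS linkage, either as the primary outcome or as a key co-reported workstream 1 outcome. Analyse it with the same matching and instrumental-variable methods, by week of gestation.
- If death before discharge stays primary, restate the primary objective as survival to discharge and make 1-year survival a key secondary objective.
- State that discharge means final discharge from neonatal care, across transfers and step-down.
- Reconcile 365 days of age in the linkage text with 1 year of corrected age in the economic evaluation, and give one definition for both workstreams or say why they differ.

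The cost is mainly rewording plus one further analysis on data already planned. The 365-day result must wait for linkage, and the number and characteristics of unlinked babies must be reported by birth setting. Keeping death before discharge in the report preserves comparability with the earlier survival-to-discharge evidence.

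### Matching and 2SLS do not remove selection by survival, so the claim of unbiased 2SLS estimates is too broad for secondary outcomes that death can preclude

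*Protocol article*

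**What the plan says.** Under Workstreams 1 and 3, the Clinical outcomes paragraph states: "The primary outcome for workstream 1 is death before discharge from a neonatal unit". It adds: "We expect a within-unit mortality percentage of approximately 5% in this group". The workstream overview keeps the two kinds of outcome apart: unit type at birth is studied for whether it "influences the primary outcome (mortality) and secondary outcomes (morbidities) in babies born at 27–31 weeks gestation".

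The secondary outcomes are given as examples: BPD, retinopathy needing laser treatment, and the worst cranial ultrasound finding. Special attention is promised to growth, blood stream infection, patent ductus arteriosus, and "time to full enteral feeds, time to breast feeding at initiation and breast feeding at discharge".

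The Statistical methods paragraph explains why adjustment is needed: "the difference in mean outcomes of babies born in either setting with an NICU or an LNU" may be biased if the babies differ at baseline. The remedies are propensity-score matching for measured confounding and 2SLS for unmeasured confounding. The instrumental-variable paragraph concludes that, provided the instruments are valid, 2SLS gives unbiased estimates of the effect of place of birth on outcomes. It does not restrict this to particular outcomes.

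The article does not say which babies form the denominator for a morbidity, or how a death before the outcome is handled.

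**The concern.** BPD, laser-treated retinopathy, the two feeding times and breast feeding at discharge are observable only in babies who live long enough. A perfect match or a valid instrument makes the groups comparable at birth. It does not make the survivors comparable, because survival occurs after exposure and may depend on it. For time to full feeds the difficulty is sharper: a contrast of means, or a 2SLS model, has no value to use for a baby who dies first.

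Differential mortality is plausible on the article's own account. It reports better survival with NICU care at 23–26 weeks and asks whether place of birth matters at 27–31 weeks. If one setting saves additional fragile babies, its survivors may look less healthy for that reason alone.

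The abstract places key morbidities beside survival in the primary objective, at each week of gestation. The Background says that cost-effectiveness and family satisfaction should take over as the main drivers if key clinical outcomes do not differ significantly. A morbidity excess produced by survival could therefore be weighed against a real survival gain when recommendations are drawn up.

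**Working it through.** **The plan's own figures.** "With approximately 6000 babies per year in England meeting our criteria" over the five birth years 2014–2018 gives 6000 × 5 = 30 000, which agrees with "the study is expected to include data on approximately 30 000 babies". At 5% mortality this is 30 000 × 0.05 = 1500 deaths. No mortality by setting or week and no morbidity rate is given, so every such rate below is an assumption.

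**Set-up.** Suppose the groups are perfectly balanced at birth and setting has no true effect on morbidity. Let mL and mN be mortality in LNU and NICU, with mN ≤ mL. Let p be the morbidity risk of babies who survive in either setting, and q the risk of the extra NICU survivors. Assume no baby would survive in an LNU but die in a NICU.

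- LNU survivors: risk p.
- NICU survivors: risk [p(1 − mL) + q(mL − mN)] / (1 − mN).
- Survivor-only difference: (q − p)(mL − mN) / (1 − mN).
- Morbidity counted over all babies: difference q(mL − mN).
- Death or morbidity over all babies: difference −(1 − q)(mL − mN).

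The survivor-only difference is zero when mL = mN or q = p. It cannot exceed (mL − mN)/(1 − mN), which is roughly the mortality difference.

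**Worked case.** With mN = 4%, mL = 6%, p = 10%:
- q = 50%: (0.094 + 0.010)/0.960 = 10.83%, an excess of 0.83 points.
- q = 100%: (0.094 + 0.020)/0.960 = 11.875%, an excess of 1.875 points.

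**Range.** Survivor-only NICU excess in percentage points, for q = 50% to q = 100%:

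| p | Deaths 4.5% vs 5.5% | Deaths 4% vs 6% |
|---|---|---|
| 5% | 0.47 to 0.99 | 0.94 to 1.98 |
| 10% | 0.42 to 0.94 | 0.83 to 1.875 |
| 30% | 0.21 to 0.73 | 0.42 to 1.46 |

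For p = 10%, assume 15 000 babies per setting, two-sided 5% tests, no clustering and no matching loss. The chance of a significant difference with no true morbidity effect is then 21% to 74% for the 1-point mortality gap, and 63% to nearly 100% for the 2-point gap.

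**A modest case, per 1000 babies.** Deaths 50 (LNU) and 40 (NICU), p = 20%, q = 70%:
- Survivors: 190/950 = 20.0% against (190 + 7)/960 = 20.5%.
- All babies: 19.0% against 19.7%.
- Death or BPD: (50 + 190)/1000 = 24.0% against (40 + 197)/1000 = 23.7%.
- Standard error of the survivor difference with 14 250 survivors per setting: √(2 × 0.2 × 0.8 / 14 250) = 0.47 points, so the excess is about 1.1 standard errors.

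**Behaviour of the proposed measures.** Under the same null, the death-or-morbidity difference is never against the setting with fewer deaths. With 4% against 6% it is −1.00 point at q = 50% and 0.00 at q = 100%. For breast feeding at discharge, let g be the chance that an extra survivor is breast feeding. The difference in alive and breast feeding over all babies is g(mL − mN), which is never negative.

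**The case against.** The article is a condensed account, and its analysis plan is not shown. Denominators and competing events are commonly settled there, and their absence here is not an error. A reader might infer that morbidities will be analysed in survivors only, or with deaths ignored. The text does not say so. The sentence about mean outcomes explains why adjustment is needed; it does not fix an analysis for each morbidity. This objection stands against any claim about the handling of deaths. It does not rescue the unbiasedness statement, which is made for outcomes generally and is not true of outcomes that death can preclude.

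A reader might also infer that the setting with better survival will show more morbidity. The documents do not support that. The bias needs both a mortality difference and extra survivors at above-average risk, and a modest true benefit can outweigh it. For p = 10% and 4% against 6% deaths, a NICU risk ratio below about 0.92 (q = 50%) or 0.81 (q = 100%) among babies who survive in either setting reverses the excess.

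Three further limits stand. Counting BPD over all babies involves no selection by survival: 19.0% against 19.7% is a real total effect, to be read beside mortality. Scoring deaths as not breast feeding would favour the setting with better survival. Blood stream infection, patent ductus arteriosus and cranial ultrasound findings can be recorded in babies who later die.

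Finally, composites dilute. In the modest case, a 1.0-point mortality benefit (about 4 standard errors with 15 000 per setting) shrinks to 0.3 points in the composite. That is a reason to add composites beside the separate outcomes and not to replace them.

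**Conclusion.** The point holds for BPD, laser-treated retinopathy, time to full enteral feeds, time to breast feeding and breast feeding at discharge. For these, matching and 2SLS address selection into a setting but not selection by survival, and the article's unbiasedness statement is too broad.

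The likely size is small. It is about 0.2 to 1.0 points for an assumed 1-point mortality difference, and 0.4 to 2.0 points for a 2-point difference, over the morbidity risks tried (5% to 30%, with q from 50% to 100%). In a cohort of about 30 000, an artefact of that size can reach significance for a less common morbidity, although clustering and matching loss would reduce that chance. The mortality split, the morbidity risks and the equal allocation between settings are all assumed. The size may differ between gestational weeks, but the article gives no rates from which to calculate it.

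**What to change.** 1. In the instrumental-variable paragraph, limit the claim of unbiased 2SLS estimates to outcomes defined for all babies.
2. For BPD and treated retinopathy, add a NICU against LNU comparison of death or the morbidity, with both components shown.
3. For time to full enteral feeds and time to breast feeding, analyse the cumulative incidence of reaching the milestone with death as a competing event.
4. For breast feeding at discharge, report alive and breast feeding at discharge over all babies.
5. Present survivor-only figures as descriptive, beside the mortality difference.

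This takes a few lines of outcome definition and modest extra analysis. Deaths are already captured as the primary outcome and through the linked ONS records, so no new data are needed. The downside is that composites mix death with less serious events, which is why the components must stay visible.
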